## Abstract

**Background:**

Infantile colic is a common condition during early childhood affecting around one of six newborns. The condition is characterized by inconsolable crying and fussing in otherwise healthy and thriving infants. The most used definition is excessive crying for at least three hours a day for at least three days for at least three weeks. The cause of colic is still unknown although many hypotheses and thereby many different treatment modalities have been investigated. Chiropractic care is used increasingly in treatment of infants, including for infantile colic, although the evidence worldwide is sparse. A randomized, controlled trial was designed to evaluate the effect of chiropractic treatment on infantile colic. This paper describes the protocol as well as results from a pilot study examining the acceptability and feasibility of the intervention.

**Method:**

The study is designed as a single-blind randomized, controlled trial. The invited families are residents on the Island of Funen and information about the project is distributed from the maternity wards and health visitors. Children at the age of 2–14 weeks with unexplained excessive crying are screened for eligibility and recruited by the primary investigator through home visits. Eligible children are then randomized to chiropractic treatment or control. All children attend in the chiropractor clinic two times a week for two weeks. The parents are unaware of their child’s allocation during the project period. The primary outcome measure is change in daily hours of crying based on the parental diaries.

The study intends to include 200 children, and the intervention has, during a pilot study, been found acceptable and feasible among families with newborns.

**Discussion:**

In a single-blind randomized controlled design we will evaluate the effectiveness of chiropractic treatment on infantile colic. The study will contribute to determine the effect of chiropractic treatment on infantile colic in an area where limited evidence exists. Furthermore, the study aims to explore if subgroups of children with suspected musculoskeletal problems will benefit more from the intervention than others. If they obtain better results, this could imply the need for stratified care.

**Trial registration:**

Clinicaltrials.gov and Identifier: NCT02595515 (registered 2 November 2015).

**Electronic supplementary material:**

The online version of this article (10.1186/s12998-018-0188-9) contains supplementary material, which is available to authorized users.

## Background

Infantile colic is a common condition during early childhood affecting on average one of six newborns. The condition is characterized by inconsolable crying and fussing in otherwise healthy thriving infants. The most used definition is excessive crying for at least three hours a day for at least three days a week for at least three weeks. The babies are between two and four months, with a mean onset of colic at two weeks and an average duration of symptoms of four to five months [1, 2].

Although the symptoms in most cases cease at the age of four to five months and very rarely indicate serious underlying disease, unexplained crying is a common cause for seeking professional medical advice [3]. This may reflect the burden and stress experienced by the families of a colicky child [4, 5]. Having a colicky child has been associated with higher risk of maternal postpartum depressive symptoms and a high level of distress even after the colic has stopped [6–8]. In the extreme, inconsolable crying can lead to child abuse, and has been associated with baby shaken syndrome [9, 10]. Furthermore, even though colic is considered a ‘benign and self-limiting’ condition, an increasing number of studies indicate there may be sequelae to this condition, including later developmental and behavioral problems, such as sleeping disorders, sensory processing abilities, lack of concentration, hyperactivity and temper tantrums [6, 11–13].

The aetiology of infantile colic still remains to be established. The original meaning of the word ‘colic’ is ‘large intestine’ which implies that a cause in the digestive or gastrointestinal system, resulting in painful contractions of the gut, has traditionally been suspected. Hypotheses regarding the cause of excessive crying have also frequently involved the gastrointestinal system, e.g. immaturity [14], allergy towards cow’s milk [15], transient lactose intolerance [16], intestinal microflora [17] and motility dysfunction [18]. Other hypotheses include disturbances in the parent-child relationship [19], factors related to the pregnancy and birth [20, 21] or merely the extreme of normal crying [22]. Based on the different aetiological hypotheses many different interventions have been performed but the results are ambiguous, and imply that colic may have a multifactorial aetiology with the need for a more stratified treatment approach [23–26].

Another commonly believed theory is that these children cry because of pain that origins from the musculoskeletal system [27], and thus manipulative therapy could be indicated as part of the solution.

Worldwide, children, including infants, are increasingly diagnosed and treated in chiropractic clinics, [28, 29], a tendency also seen in Denmark where chiropractic visits for infants have more than doubled over the last ten years with infantile colic or excessive crying being the main cause [30, 31]. In contrast to this, the effect of chiropractic treatment on infantile colic has only been investigated in few randomized, controlled trials, and the results are ambiguous. A Cochrane review regarding manipulative therapies for infantile colic identified six randomized trials representing a total of 325 infants [27]. Of the six studies, five showed a positive effect on daily hours of crying, and one found no difference when compared to the natural cause of infantile colic. However, in general there were methodological weaknesses, since the studies were generally small, and furthermore in most studies parents were aware if the child was treated or not, which increases the risk of a placebo effect in the intervention group. Since chiropractic treatment of infantile colic is widely used, there is a need to investigate the effectiveness on the condition in a larger scale study with parental blinding [27].

A randomized controlled trial was designed to evaluate the effect of chiropractic treatment on crying time and other symptoms associated with infantile colic. Furthermore, the study aims to explore if subgroups of children with suspected musculoskeletal problems will benefit more from the intervention than others. This article will describe the protocol as well as the results from a pilot study examining the acceptability and feasibility of the intervention.

## Method

### Study design

Multicenter single-blind randomized controlled trial.

### Study setting and participants (Fig. 1; Additional file 1)

#### Recruitment

The invited families are residents on the Island of Funen (approx. 500.000 inhabitants). Information about the existence of the project is given by: 1) health visitors, 2) general practitioners, 3) written information about the study in a folder given to all women that has given birth at Odense University Hospital, 4) the chiropractic clinics participating in the study and 5) advertisements in local media and on Facebook. Parents are encouraged to contact the primary investigator (PI) by telephone, where she will screen the child for in- and exclusion criteria. If inclusion criteria seem to be fulfilled, and the parents agree to participate, a more thorough interview is arranged to take place in the home of the family.

**Fig. 1 Fig1:**
[figure not shown]
Study flow chart and time lime for participants

#### Visit 1

At the first visit, the PI, who is a medical doctor, assesses the child for eligibility and provides oral and written information (Additional file 2) regarding the project.

At the first visit the PI furthermore completes an interview-based questionnaire (Additional file 3) with the purpose to collect information about baseline variables and potential clinical predictors and confounders. The choice of variables was based on knowledge from existing literature [6–8, 19–21, 23, 27, 32] and focus group discussions with chiropractors and health visitors. Questions concerns the child’s crying pattern, birth weight and length, current weight and length, feeding mode and pattern, burps, regurgitation, bowel movements, anamnestic and objective signs of musculoskeletal problems (e.g. favorite side), previous treatment of the colic or other condition/disease, the mother’s health and use of medication, the parents’ level of serious mental stress during pregnancy and after the birth, mental stress of the parents in everyday life, educational level and cohabitation status of the parents, smoking status of the parents, siblings with history of colic, the parents’ belief regarding the effect of chiropractic treatment on colic, and selected factors related to pregnancy and birth. With consent of the parents pregnancy and birth related factors will also be collected in the mother’s hospital record, e.g. mother diagnosed with depression, gestational age at birth, durations of the different stages in birth, abnormal presentation in the birth canal and interventions in birth.

If the parents’ consent to participate with their child (Additional file 4), they are introduced to a diary for use during the study (Additional file 5). This diary represents the parents’ structured notes of the child’s behavior, a validated method that has proved to be reliable as an objective recording of the child’s behavior and symptoms [33]. The parents are thoroughly instructed to record the child’s behavior throughout every 24 h during the whole project period. ‘Time rulers’ representing every 24 h divided in time intervals of fifteen minutes are filled out with different symbols representing the child’s behavior, including the amount of inconsolable crying (crying without an obvious reason that cannot be comforted by any attempt of the parents), the time the child needs to be held and rocked to limit crying (crying without no obvious reason that is only partly and briefly limited if the child is constantly held/rocked), the time the child is awake and content, and the time spent sleeping, feeding patterns and bowel movements. Consolable crying with an obvious reason that is easily comforted as e.g. hunger or a soiled diaper is registered as ‘awake and content’. To limit recall bias and make the registration as precise as possible the parents are advised to fill in the diary several times a day. Baseline registration of the crying pattern is done for at least three days whereupon a second visit from the PI is scheduled.

#### Visit 2

At the second visit, any difficulties filling out the daily diary is identified and the parents’ assessment of the crying pattern is evaluated in a second interview-based questionnaire (Additional file 6). Eligible children are then randomized, and an appointment is booked in one of the participating chiropractic clinics (parents’ choice). Four chiropractic clinics with seven chiropractors participate in the study, and all the chiropractors have a special interest and experience in pediatric practice. The treating chiropractors have been working from nine years to more than thirty years in the field.

### Inclusion criteria

Infants aged 2 to 14 weeks with symptoms of infantile colic defined as otherwise healthy thriving infants with episodes of excessive crying that last at least three hours a day, for at least three days a week in the past two weeks. During the crying episodes the child cannot, or only briefly and partly, be comforted. The type and duration of the crying episodes is assessed by the parents after thorough instruction by the PI as described above (*visit 1*). Except from these crying episodes, the child must show normal development and gain at least 150 g a week (it is though considered normal that the child in the first week of life loses up to 10% of the birth weight, which is hereafter regained).

### Exclusion criteria

The child cannot have symptoms of disease, suffer from a current disease or have sequelae from a former disease. The child cannot have contraindications for chiropractic treatment, e.g. certain congenital malformations, or have received chiropractic treatment for colic previously. Concomitant treatment for colic (e.g. reflexology) is not permitted during the project period.

### Randomization and blinding

The allocation occurs through a 1:1 ratio by a predetermined restricted randomization scheme. The participants are stratified according to their age at enrollment (2–6 weeks; 7–10 weeks; 11–14 weeks) and the treating chiropractor. The eligible participants are randomly assigned in blocks of 4 to 6, according to computer-generated random numbers, to be enrolled in either the intervention or control group.

The computer generated block randomization was administered by a research assistant, not otherwise involved in the outcome measurements or the intervention. The research assistant then wrote the consecutive letters A and B on separate pieces of paper and then placed them in sealed opaque envelopes, which were given to each chiropractor. To take the above mentioned stratification into account the procedure was repeated and a different list of group allocation was made for each age level and each chiropractor in the study. When a child is randomized and an appointment booked, the PI informs the clinic of the next randomization number for that specific chiropractor and age group (which is a coded number not revealing group allocation). Only the chiropractor has the list that reveals if that certain randomization number means allocation to intervention or control group.

Hence, the intervention in this trial makes blinding of care providers impossible. The parents are blinded to their child’s allocation group during the project period. To uphold blinding of the randomization, all parents leave the chiropractor’s consultation room for a few minutes after history taking and examination, while the treatment is (or is not) carried out. For the analyses, the coding of intervention and control groups will be concealed from the PI and the statisticians performing the analyses. The randomization code will not be broken until the analyses are completed.

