### Intervention

The study is pragmatic and assesses the effect of the treatment the clinician finds indicated, rather than a standard treatment. Therefore the study does not investigate a specific manual treatment, but investigates the whole chiropractic intervention with individual attention to the children’s potential biomechanical dysfunctions, as described below.

All children attend the chiropractor clinic two times a week for two weeks. After the fourth visit the parents continue their registration in the diary as an ‘after registration’ for at least three days, and fill out the final questionnaire including questions regarding the status of their child’s colic, bowel movements, burps, regurgitation and their belief regarding group allocation (Additional file 7). Hereafter an information visit takes place at the chiropractic clinic, where the parents hand in the completed diary and questionnaire and are informed whether their child has been in the treatment or control group. Children in the control group are then offered a similar treatment free of charge as the intervention group, if symptoms have not subsided, a strategy to improve adherence to the study.

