#### The control group receives

Medical historyExamination without motion palpation of the joints, as this could approach mobilization. Examination includes undressing the child and observing if there are notable asymmetries of limb orientation and development, and distortions of the head, spine and body shape that could indicate a biomechanical dysfunction (related to muscles, ligaments and/or joints). Furthermore, the examination includes a mental and neurological statusBased on the medical history and examination the clinician estimates whether the child’s symptoms are likely to be related to a biomechanical dysfunctionPragmatic advice such as cycling with the child’s legs and changing the position of the child’s head from one nap to the nextAt the last visit, the chiropractor assesses if the child possibly can benefit from a similar treatment as given in the intervention group.

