#### The intervention group receives

Medical historyFull examination, including motion palpation of the joints. To diagnose a biomechanical dysfunction examination includes static and movement palpation, observation of notable asymmetries of limb orientation and development, and distortions of the head, spine and body shape as well as exploration of muscular and ligamentous tonus and movement restrictions in articulations. Furthermore, mental and neurological status.Based on the medical history and examination the clinician estimates whether the child’s symptoms are likely to be related to a biomechanical dysfunction. This assessment is done before motion palpation of the joints and reassessed again after the motion palpation.Manual treatment will include manipulation or mobilization of the spine and/or the extremities as indicated by the child’s potential biomechanical dysfunctions, including movement restriction, tenderness or an obvious asymmetry in the muscles or joints. If no biomechanical dysfunction is detected mobilization is carried out where all the joints in the spine are lead through their normal range of movement.Specific advice directed towards any biomechanical dysfunction, and exercises that supports the effect of the manual treatmentAt the last visit the chiropractor assesses if the child’s course of treatment is completed or whether continued treatment is indicated

The manual therapy in the intervention group is thus administered when there is biomechanical dysfunction in one or more joints which the treating clinician relates to the child’s symptoms. In general, the treatment technique for restricted movements in joints in this age group is a very light short-term pressure with fingertips and gentle massage in case of hypertonic muscles.

The frequency and content of treatments is intended to resemble pragmatic daily clinical practice in order to optimize the treatments by individualization and to make the results generalizable.

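### Parents leave the room only after the examination, yet the examination differs by arm, so the masking step as written leaves a visible difference uncovered

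*Protocol article*

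**What the plan says.** - **When parents leave.** Protocol article, Randomization and blinding: "all parents leave the chiropractor’s consultation room for a few minutes after history taking and examination". The absence covers the time in which treatment is or is not given. The same section states that chiropractors cannot be blinded and that parents are blinded throughout the project period.
- **Control examination.** The section on the control group describes an examination "without motion palpation of the joints, as this could approach mobilization". It consists of undressing the child, looking for asymmetries and distortions, and a mental and neurological status.
- **Intervention examination.** The section on the intervention group lists a full "examination, including motion palpation of the joints", with exploration of muscle and ligament tonus and of restricted movement. On the judgement of biomechanical dysfunction it adds: "This assessment is done before motion palpation of the joints and reassessed again after the motion palpation". Manual treatment is a separate, later item.
- **Last visit.** In the control arm, "the chiropractor assesses if the child possibly can benefit from a similar treatment as given in the intervention group". In the intervention arm, the chiropractor judges instead whether the course is finished or should go on.
- **Outcome recording.** Intervention section: "After the fourth visit the parents continue their registration in the diary as an ‘after registration’ for at least three days". The final questionnaire also asks parents about "their belief regarding group allocation". Diary and questionnaire are handed in at a later information visit, where the allocation is disclosed.
- **Weight placed on blinding.** The Discussion lists parental blinding among the four main strengths. The Background names its absence as a weakness of most earlier trials.

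**The concern.** The primary outcome is the change in crying hours that parents record themselves. With unblinded chiropractors, parental blinding is the main protection against expectation affecting that record. It depends on parents not seeing anything that differs by arm.

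The exit from the room is meant to achieve this, but it is placed after the examination. Read together, the three sections have the parents present while a child in one arm is palpated joint by joint and a child in the other is not. The protocol leaves motion palpation out of the control arm because it comes close to mobilization, so by its own reasoning this is not a trivial difference.

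A parent who suspects the allocation may record crying differently. Control families are also offered the treatment free of charge afterwards if symptoms persist, which could colour the record of a parent who suspects control. If the reporting shift differs between arms, it goes straight into the treatment comparison, and no later analysis can take it out of the diaries with confidence.

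**Working it through.** **1. The sections side by side**

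| Step | Control | Intervention | Parents, as written |
|---|---|---|---|
| History | yes | yes | present |
| Observation of asymmetry; mental and neurological status | yes | yes | present |
| Motion palpation | omitted on purpose | yes, listed under examination | present, since they leave after the examination |
| Tonus and movement-restriction testing | not named | yes, listed under examination | present, for the same reason |
| Manual treatment | no | yes | out |

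The exit masks the last row only. Advice also differs by arm (general in control; directed at dysfunction, with exercises, in intervention). It has to reach the parents, so no change to the exit can mask it.

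**2. The plan's own sample size**

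Inputs from Sample size: difference 1 h, SD 2.5 h, alpha 0.05 (taken as two-sided), power 80%, 1:1 allocation.

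n per arm = 2 × (1.960 + 0.842)² × 2.5² / 1² ≈ 98.1, rounded up to 99, so 198 in total. The t-distribution version gives 99.1, hence 100 per arm and 200 in total. The stated 200 is reproduced. Power with 100 per arm is 80.7% (t-test 80.4%).

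**3. What a reporting shift would do (illustration; the shift sizes are assumed)**

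SE of the difference = 2.5 × √(2/100) = 0.354 h. With no true effect and a differential shift b between arms, the chance of a two-sided significant result is

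1 − Φ(1.96 − b/SE) + Φ(−1.96 − b/SE).

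| Shift b (h/day) | b/SE | Chance of significance |
|---|---|---|
| 0 | 0 | 5% |
| 0.10 | 0.28 | 5.9% |
| 0.25 | 0.71 | 10.9% |
| 0.50 | 1.41 | 29.3% |

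**4. Where b would come from**

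Suppose that in each arm a share c of parents guesses correctly and a share w wrongly, and each guess moves the recorded change by d hours in the direction of the guess. Then b = 2(c − w)d, because wrong guesses offset right ones. With c − w = 0.1 and d = 0.25 h, b = 2 × 0.1 × 0.25 = 0.05 h. With c − w = 0.5 and d = 0.5 h, b = 2 × 0.5 × 0.5 = 0.5 h. The documents give none of c, w or d, so this tenfold range reflects the chosen inputs and says nothing about the trial itself.

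**The case against.** The strongest reply is that a visible difference is not the same as a recognised one. Each family sees one arm only, and children already treated by a chiropractor for colic are excluded. Both arms have a history, a hands-on visit with the child undressed, advice, and a few minutes with the parents outside. To read palpation as a sign of allocation, a parent must know that it belongs to the active arm, and the parent information (Additional file 2) is not shown. This stands: a reader might infer that parents can work out the allocation, but the documents support only that some may be able to. Nor is the control examination mere observation, since it includes a mental and neurological status.

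Second, the dysfunction judgement is made before palpation and again after it, so palpation is a separable step that could follow the parents' exit. That is possible, but the text does not say so. It lists palpation under examination and places the exit after examination.

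Third, a reader might infer that the last-visit assessment reveals the arm just before the post-treatment diary. The protocol says only that the chiropractor assesses; it does not say that parents are told. Disclosure is planned for the information visit, and telling them earlier would conflict with the blinding statement. "Last visit" most naturally means the fourth visit, but could be read as the information visit. So this supports a safeguard and is not a demonstrated leak.

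Fourth, the plan already asks parents for their belief about allocation before disclosure. That measures unblinding without preventing it. How the answers are tabulated can be left to the statistical analysis plan and is not criticised here.

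**Conclusion.** The point holds as a gap in the masking procedure. As written, the parents' exit does not cover an examination step given in one arm only, and the same parents record the primary outcome. They may therefore be able to infer the allocation.

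The size is unknown. Under 100 per arm, SD 2.5 h, a two-sided 5% test and no true effect, assumed differential shifts of 0.1, 0.25 and 0.5 h/day raise the chance of a significant result from 5% to about 6%, 11% and 29%. These figures show how sensitive the test is to a shift; they do not estimate one. A reader might go on to infer that the bias is a sizeable share of the 1-hour target difference. The documents do not support that, because they give neither the share of parents who would guess nor the effect of guessing on the diary.

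The correction is cheap, and diaries already affected cannot be repaired afterwards. It is worth making, without implying that the blinding has failed.

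**What to change.** 1. In Randomization and blinding, and in the sections on what each group receives, state that in both arms parents leave after history taking and the examination elements common to both arms; that motion palpation and tonus/movement testing are done only while they are out; and that the absence lasts equally long in both arms. If palpation is already done in the parents' absence, it is enough to say so and reconcile the sections.
2. As a safeguard, state that the arm-specific last-visit assessment is recorded but not told to parents until the diary and final questionnaire are handed in at the information visit.

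**Cost.** Parents are out of the room slightly longer. Recruitment is under way, so a minor amendment goes to the ethics committee and the seven chiropractors need an instruction. Children already examined are not covered, so the date of the change should be recorded. The difference in advice remains, because parents must receive it.
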